### Withdrawal from the Trial

Subjects are free to discontinue the trial at any time without giving their reasons.

Additionally, the Investigator may withdraw a subject from study treatment at any time if considered to be in the subject’s best interest. Withdrawal from study treatment is mandatory in the following situations:

- Pregnancy [(see Section 7.9.2)](#_Pregnancy_and_In)
- Initiation of treatment with an investigational agent or a prohibited concomitant medication [(see Section 6.4.2)](#_Non-permitted_Medicines)
- Initiation of treatment with another (approved or non-approved) disease modifying therapy for MS
- Common Terminology Criteria for Adverse Events (CTCAE) grade IV lab abnormalities or grade IV ‘related’ serious adverse events [(see Appendix C)](#_Appendix_C-_Common_)
- Adverse events leading to prolonged dose reduction of more than two weeks
- Protocol violations, including non-compliance and lost to follow-up
- Intercurrent illness or significant worsening of previous illness
- Administrative reasons
- Withdrawal of the subject’s consent

In case of premature withdrawal from the study treatment, the assessments scheduled for the Week 24/Exit visit should be performed. [(see Section 7.2.2.3)](#_Week_24/Exit_Visit)

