### Follow-up for Discontinued Subjects

If a subject fails to return for follow-up, attempts should be made to contact the subject to determine if the reason for not returning is an adverse event. If a subject withdraws his/her consent to continue in the trial, an attempt must be made to follow-up with the subject.

If treatment is prematurely discontinued, the primary reason for discontinuation must be recorded in the appropriate section of the e-CRF, and all efforts will be made to complete and report the observations as thoroughly as possible. If, for any reason, a subject withdraws or is withdrawn from the trial, every attempt will be made to conduct a follow-up visit with the subject (with all assessments for Week 24/Exit to be completed) [(see Section 7.2.2.3)](#_Week_12/Exit_Visit). Also, all ongoing adverse events will be followed until resolution or at least a period of four weeks ± four days from the last treatment date. After three documented attempts for the four week follow-up telephone call and contact has not been made, subject is considered lost to follow-up.

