### Definition of End of Trial

This trial will be considered as completed after:

- all enrolled subjects, who have received at least one dose of Rebif® have completed all scheduled visits (including all prematurely discontinued subjects who should undergo at least the Week 24/Exit visit and the four-week, post-treatment telephone call);
- follow-up of all subjects with ongoing adverse events at the conclusion of treatment has been addressed; [(see Section 7.9.1.6)](#_Monitoring_of_Subjects)
- all data discrepancies have been resolved;
- the database has been locked; and
- the study site has undergone a final closure visit (usually four to six weeks after the database lock).

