#### Week 24/Exit Visit

**RRMS Subjects**

The following procedures and assessments will be performed at the Week 24/Exit visit or following early termination of a subject from the trial:

- Recording of adverse events and concomitant medications/procedures
- Laboratory Assessments (Chemistry, Hematology, ferritin, transferrin, CBC, LFTs, platelets, uric acid)
- A blood sample will be collected for analysis of thyroid function tests.
- Physical examination unrelated to MS, including height, weight and vital signs [(see Section 7.2.6.1)](#_Physical_Examinations)
- Neurological assessment (full exam, not including EDSS) [(see Section 7.2.6.2)](#_Neurological_Assessments)
- Blood collection for Immunological Samples
- MRI
- For female subjects of childbearing potential, a urine pregnancy test, to be performed locally at the study site
- Reason for termination (if subject terminates early)
- Drug accountability

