##### MRI Acquisition

MRI exams of the brain will be performed on a 3T GE Signa LX Excite 12.0 scanner at the Buffalo Niagara MRI Center, located within Buffalo General Hospital, [name]. In addition to localizer/scout images and calibration images, the following scans will be acquired: dual echo proton density and T2-weighted image (WI), 3D-inversion recovery fast-spoiled-gradient recalled (IR-FSPGR), T1-WI, spin-echo (SE) T1-WI with and without gadolinium (Gd) contrast, fast attenuated inversion recovery (FLAIR), gradient echo (GRE) T1-weighted magnetization transfer imaging (MTI) with and without saturation pulse and susceptibility weighted imaging (SWI). Conventional 2D scans (PD/T2, FLAIR, and T1 SE pre- and post-contrast) will be acquired with consistent voxel size (64 slices 3mm slice thickness, with FOV = 25.6, matrix = 256 x 256 and phase FOV =.75), and slice selection (oblique axial images parallel to the subcallosal plane). MTI will be acquired with 4mm slice thickness, FOV = 25.6, phase FOV = .75, matrix 256x256, TR = 50, TE = 6 and FA = 10. 3D GRE SWI will be acquired with 2mm slice thickness, FOV 25.6, matrix 512x256, phase FOV = .75.

Patients with MS will receive a single dose (0.1 mmol/kg) gadolinium contrast injection prior to the FLAIR scan, which will be immediately followed by the T1 SE post contrast scan. The FLAIR scan is unaffected by the contrast and is used to provide a consistent time delay between contrast injection and post-contrast imaging. Normal control participants will not receive contrast injection.

All participants will be positioned in the scanner to maximize comfort and minimize head movement. The nasion landmark will be used to position the head in the isocenter of the magnetic field.

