### Pregnancy and In Utero Drug Exposure

Only pregnancies considered by the Investigator as related to study treatment (e.g., resulting from a drug interaction with a contraceptive medication) are considered AEs. However, all pregnancies with an estimated conception date during the period defined in [Section 7.9.1.5](#_Definition_of_Serious) be recorded in the AE section of the e-CRF. The Investigator must notify the Sponsor in an expedited manner of any pregnancy using thePregnancy Report Form (Part I), which must be transmitted according the same process as described for SAE reporting in [Section 7.9.1.11](#_Procedure_for_Reporting)*.*

Investigators must actively follow up, document and report on the outcome of all these pregnancies, even if the subjects are withdrawn from the trial. The Investigator must notify the Sponsor of these outcomes using the Pregnancy Report Form (Part II), and also must complete the SAE Report when the subject sustains an event and the Parent-Child Fetus Report Form when the child/fetus sustains an event.

Any abnormal outcome must be reported in an expedited manner as described in [Section 7.9.1.11](#_Procedure_for_Reporting), while normal outcomes must be reported within forty-five days from the date of delivery.

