## Description of Statistical Analyses

### General Considerations

All statistical tests will be two-tailed and considered significant at an α=0.05 level of significance; all confidence intervals will be two-sided 95% confidence intervals.

Dropouts, if any, will be examined. Subjects who stop the Medicinal Product will be asked to remain in the study and will be analyzed with the intention to treat, but adding a covariate that alternative therapies have been given. Individual data will be analyzed. No imputation of missing data will be performed.

T-tests and chi-square tests for independent samples will be used for comparison of demographic and clinical characteristics between RRMS patients and HC.

VW-MTR and SWI spatial distribution analysis will be conducted directly on the images. Analysis of MRI measures may require a variance stabilizing transformation, if skewness is observed in their assessments. Each of the MRI parameters will be examined and appropriate transformations will be applied, if necessary.

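### An RRMS subject taken off Rebif because of pregnancy is directed to an exit MRI with gadolinium, and no pregnancy exception is stated

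*Protocol*

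**What the plan says.** Pregnancy is the first item in the Section 5.4.5 list of situations in which withdrawal from study treatment is mandatory. The same section closes with the general rule: "In case of premature withdrawal from the study treatment, the assessments scheduled for the Week 24/Exit visit should be performed".

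Section 5.4.7 adds a similar direction for subjects who leave the trial, whatever the reason: "every attempt will be made to conduct a follow-up visit with the subject (with all assessments for Week 24/Exit to be completed". Section 5.4.9, in defining the end of the trial, refers to "all prematurely discontinued subjects who should undergo at least the Week 24/Exit visit".

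The RRMS list under the Week 24/Exit Visit (Section 7.2.2.3) opens: "The following procedures and assessments will be performed at the Week 24/Exit visit or following early termination of a subject from the trial". It contains MRI and, further down, a urine pregnancy test for women of childbearing potential. No condition links the two. Appendix A shows both at the same visit.

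MRI Acquisition (within Section 7.2.6) states: "Patients with MS will receive a single dose (0.1 mmol/kg) gadolinium contrast injection prior to the FLAIR scan". The only exemption it gives is: "Normal control participants will not receive contrast injection".

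The pregnancy item in 5.4.5 points to Section 7.9.2, which deals with notification and outcome: "Investigators must actively follow up, document and report on the outcome of all these pregnancies, even if the subjects are withdrawn from the trial". It does not mention MRI, contrast or the exit visit. Section 6.4.4, Special Precautions, is marked not applicable.

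**The concern.** A general exit rule, sensible for most withdrawals, also covers the one withdrawal reason that is itself a pregnancy. The protocol treats pregnancy as grounds to stop the drug and then, by default, sends the same subject to a scan at which patients with MS are given contrast for research purposes. Nowhere does it record a decision that this is intended.

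This is a matter of subject safety, not an error in the statistical analysis. A site following the text has no instruction to omit the contrast and must depart from the protocol on its own judgement. The protocol states no gadolinium risk in pregnancy, so no size of harm is claimed here. The point is that the written rule reaches a known pregnancy without the question having been addressed.

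**Working it through.** The protocol gives no figure on this point, so there is nothing of its own to reproduce. The main check sets the sections side by side.

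**The chain for an RRMS subject who becomes pregnant on treatment**

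| Step | Source | Result |
| --- | --- | --- |
| 1 | 5.4.5, list | Study treatment must stop |
| 2 | 5.4.5, closing sentence | Week 24/Exit assessments should be done |
| 3 | 7.2.2.3, RRMS list | These include MRI, also after early termination |
| 4 | MRI Acquisition | Patients with MS receive 0.1 mmol/kg gadolinium; only controls are exempt |
| 5 | 7.9.2 and 6.4.4 | No exception |

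The closing sentence in step 2 follows the list that begins with pregnancy and excludes none of its items. Step 4 is limited neither by visit nor by pregnancy status.

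**Which section carries the point.** Section 5.4.5 concerns withdrawal from treatment, so it applies directly to every RRMS subject stopped for pregnancy. Section 5.4.7 concerns withdrawal from the trial and adds the same direction only if she also leaves. Section 5.4.9 names the visit and does not spell out its assessments. The conclusion therefore rests on 5.4.5, with 5.4.7 as an addition in some cases.

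**How often it could arise**

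Inputs:
- 25 RRMS subjects (Section 5.1.4).
- Treatment of 24 weeks.
- A contraceptive failure rate below 1% per year (Section 5.4.1), taken at its limit of 0.01.
- The number of women of childbearing potential is not given; 10 to 25 is assumed.

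Expected pregnancies = women × 0.01 × 24/52. Chance of at least one = 1 − exp(−expected).

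| Women (assumed) | Expected pregnancies | Chance of at least one |
| --- | --- | --- |
| 10 | 10 × 0.01 × 24/52 = 0.046 | 4.5% |
| 15 | 0.069 | 6.7% |
| 20 | 0.092 | 8.8% |
| 25 | 0.115 | 10.9% |

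Two cautions apply. The 1% limit defines acceptable methods under consistent and correct use, so actual failure may be more frequent; the expected count rises in proportion to the rate. In the other direction, the figures count all pregnancies, and only some would be recognised before a scan.

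**Data cost of an exception.** One exit Gd-lesion value out of 25 planned is 1/25 = 4% per affected subject.

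**The case against.** The strongest reply is that nothing here is contradictory. The protocol contains no statement that gadolinium is unsuitable in pregnancy, so without outside knowledge the gap is only an omission. The directions are also soft ('should', 'every attempt'), subjects may leave whenever they wish, and the investigator is bound by good clinical practice and the Declaration of Helsinki. The consent pages are not in this copy, and an imaging manual, if there is one, might carry a contrast precaution. The expected number of cases is well below one.

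Most of this limits the point without removing it. The soft wording means the injection is a default, not an absolute requirement. The rarity and the unstated risk limit its weight. But the default comes from a rule that is written down and covers pregnancy by its own terms, so this is more than missing detail. A precaution in another document would still leave the withdrawal text directing the opposite.

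Three stronger readings are tempting, and the documents do not support them.

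- **Two contrast injections.** Section 8.4.1 says "Subjects who stop the Medicinal Product will be asked to remain in the study and will be analyzed with the intention to treat", so a reader might infer that a subject who stops before Week 12 faces contrast at both Week 12 and Week 24. That requires her to agree to stay and the exit assessments to wait until Week 24, whereas 7.2.2.3 also places them after early termination. The protocol does not say how these provisions combine. One injection, at the exit scan, is all that can be shown.
- **Inconsistency with the controls.** Healthy controls receive neither drug nor contrast, yet must not be pregnant at entry and have urine tests at Study Day 1 and Week 24/Exit. One might infer that the protocol regards MRI itself as a reason for pregnancy testing. No text links those tests to MRI or contrast, and the criterion nearly repeats the RRMS wording.
- **Three sections all mandating the scan.** As shown above, only 5.4.5 reaches every such subject directly.

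**Conclusion.** The point holds in limited form. Section 5.4.5, read with 7.2.2.3 and MRI Acquisition, directs an RRMS subject withdrawn from treatment for pregnancy to one research contrast injection at the exit MRI, and the protocol as supplied makes no exception.

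The event is rare: 0.05 to 0.12 expected pregnancies over the trial, assuming 10 to 25 women of childbearing potential, a constant rate and the 1% per year limit. The number recognised before a scan would be lower on the same assumptions. The primary analysis is not at issue. The case for correction is that the text addresses a known pregnancy with the wrong default and the remedy is small. How strict the exception should be, including whether the MRI itself goes ahead, is for the sponsor's medical lead.

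**What to change.** - State in Section 5.4.5, Section 7.2.2.3 and MRI Acquisition, and by reference in 5.4.7, that gadolinium is omitted at any study MRI in a subject known to be pregnant.
- State that the Week 24/Exit urine pregnancy test, already scheduled, is read before contrast is given.

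No visit or test is added. For the affected subject, Gd lesion volume and VW-MTR in Gd lesions are lost at that scan and, under Section 8.4.1, are not imputed. Her lesion masks for the VW-MTR and SWI analyses would be built without the post-contrast image, unlike those of the other RRMS subjects. The primary NABT value can probably still be computed, since it is obtained in controls without contrast. The protocol does not say whether the magnetization transfer scan precedes the injection, so this should be confirmed with the imaging centre.

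The change has a limit. Week 12 has an MRI but no scheduled pregnancy test, so at that visit the exception protects only a pregnancy already known. Testing there would be an additional procedure for the sponsor to consider.

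Separately, Section 7.2.4 places the urine test at Week 12/Exit, whereas Sections 5.4.1, 7.2.2.3 and 7.4 and Appendix A place it at Week 24/Exit. This is a clerical edit and not part of the argument.

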### Replacement of Discontinued Subjects

A subject who fails to meet the protocol-specified criteria for trial entry during the screening period is a screen failure. Screen failures as well as subjects prematurely withdrawn from the trial will not be replaced and subject identification numbers will not be reallocated.

### Follow-up for Discontinued Subjects

If a subject fails to return for follow-up, attempts should be made to contact the subject to determine if the reason for not returning is an adverse event. If a subject withdraws his/her consent to continue in the trial, an attempt must be made to follow-up with the subject.

If treatment is prematurely discontinued, the primary reason for discontinuation must be recorded in the appropriate section of the e-CRF, and all efforts will be made to complete and report the observations as thoroughly as possible. If, for any reason, a subject withdraws or is withdrawn from the trial, every attempt will be made to conduct a follow-up visit with the subject (with all assessments for Week 24/Exit to be completed) [(see Section 7.2.2.3)](#_Week_12/Exit_Visit). Also, all ongoing adverse events will be followed until resolution or at least a period of four weeks ± four days from the last treatment date. After three documented attempts for the four week follow-up telephone call and contact has not been made, subject is considered lost to follow-up.

### Premature Discontinuation of the Trial

The whole trial may be discontinued prematurely in the event of any of the following:

- Sponsor’s decision that continuation of the trial is unjustifiable for medical or ethical reasons
- Slow enrollment of subjects makes it unlikely that the trial will be completed within an acceptable timeframe

If the whole trial is discontinued prematurely, the institutional review board will be informed about the discontinuation of the trial in accordance with applicable regulations.

### Definition of End of Trial

This trial will be considered as completed after:

- all enrolled subjects, who have received at least one dose of Rebif® have completed all scheduled visits (including all prematurely discontinued subjects who should undergo at least the Week 24/Exit visit and the four-week, post-treatment telephone call);
- follow-up of all subjects with ongoing adverse events at the conclusion of treatment has been addressed; [(see Section 7.9.1.6)](#_Monitoring_of_Subjects)
- all data discrepancies have been resolved;
- the database has been locked; and
- the study site has undergone a final closure visit (usually four to six weeks after the database lock).

### Medical Care of Subjects after End of Trial

After a subject has completed the trial or has withdrawn early, usual treatment will be administered in accordance with the study site’s standard of care and generally accepted medical practice and depending on the subject’s individual medical needs. Rebif® will not be provided to subjects after the conclusion of the trial. No extension trial is planned.

# Medicinal Product(s) and Other Drugs Used in the Trial

The term “Medicinal Product” refers to Rebif® 44 mcg tiw for sc injection.

## Dosage and Administration

**Rebif®**

Rebif® will be supplied in pre-constituted syringes. During the four week titration phase of Rebif®, dosages must be adjusted according to the following dose titration schedule (refer to the locally approved package insert for the administration, storage and handling instructions for Rebif®):

| **Week** | **Recommended Titration** | **Volume** | **IFN-beta-1a dose** |
| --- | --- | --- | --- |
| 1-2 | 20% | 0.1 mL | 8.8 mcg |
| 3-4 | 50% | 0.25 mL | 22 mcg |
| 5 + | 100% | 0.5 mL | 44 mcg |

Source: Rebif® Package Insert: Schedule for Rebif® dose titration.

## Packaging and Labeling

Packaging and labeling will be in accordance with applicable local regulatory requirements and applicable Good Manufacturing Process Guidelines.

## Preparation, Handling and Storage

On site, all Rebif**®** must be stored in a secure location, preferably in a temperature controlled locked refrigerator or cold room, and may be dispensed only by the Investigator or by a member of staff specifically authorized by the Investigator, or by a pharmacist, as appropriate. Any deviations from the recommended storage conditions should be immediately reported to the Sponsor and use of the Medicinal Product interrupted until authorization for its continued use has been given by the Sponsor.

Rebif® should be stored between 2°C and 8°C (36°F and 46°F) and protected from light. DO NOT FREEZE.

Please refer to the locally approved package insert for storage and handling instructions of Rebif®.

## Concomitant Medications and Therapies

### Permitted Medicines

Any concomitant medications (other than those excluded by the protocol) that are considered necessary for the subjects’ welfare and will not interfere with the Medicinal Product may be given at the Investigator’s discretion (e.g. analgesics for treatment of flu-like symptoms and corticosteroids for the treatment of relapses).

All such therapy will be recorded in the e-CRF from the time the Informed Consent Form is signed until the final post-treatment follow-up, along with medication name, dosage information, dates of administration, and reasons for use.

Concomitant medications for the following reasons should be documented in the e-CRF:

- MS related condition (e.g. pain, fatigue, bladder dysfunction, spasticity, etc.)
- Medical conditions reported in the subject’s Medical History (e.g. pain, headaches, depression, etc.)
- Prophylactic Use (e.g. flu-like symptoms, etc.)
- Self-medication (e.g. vitamins, nutritional supplements, herbal/natural products, etc.)

### Non-permitted Medicines

In line with the exclusion criteria in [(see Section 5.4.2)](#_Exclusion_Criteria), subjects may not use any investigational medications or any of the following therapies during the trial:

- Cytokine or anti-cytokine therapy
- Any interferons other than Rebif®
- Intravenous immunoglobulin (IVIg)
- Monoclonal antibodies, mitoxantrone, cytotoxic or immunosuppressive therapy including but not limited to cyclophosphamide, cyclosporin, methotrexate, azathioprine, linomide, teriflunomide, laquinimod, cladribine, total lymphoid irradiation, anti-lymphocyte monoclonal antibody treatment (e.g., natalizumab, alemtuzumab/Campath, anti-CD4)
- Chronic or monthly pulse corticosteroids
- Plasmapheresis
- Glatiramer acetate
- Telbivudine

If the administration of a non-permitted concomitant medication becomes necessary during the trial, the subject should be withdrawn from the trial. [(see Section 5.4.4)](#_Criteria_for_Subject)

Any additional concomitant therapy that becomes necessary during the trial and any change to concomitant drugs must be recorded in the corresponding section of the e-CRF, noting the name, dose, duration and indication of each drug.

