### Criteria for Subject Withdrawal

Subjects will be informed that they have the right to withdraw from the trial at any time, without prejudice to their medical care, and are not obligated to state their reason(s). Any withdrawals must be fully documented in the e-CRF and source documents and should be followed-up by the Investigator.

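### Section 6.4.2 takes a subject who switches to a non-permitted MS therapy out of the trial, while Section 8.4.1 keeps the same subject in and Section 5.4.5 ends only Rebif

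*Protocol*

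**What the plan says.** Four sections of the protocol deal with a subject who can no longer stay on Rebif alone.

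- **Section 6.4.2 (Non-permitted Medicines)** bars a list of therapies for the duration of the trial. The list includes interferons other than Rebif, glatiramer acetate, natalizumab and mitoxantrone. It then says: "If the administration of a non-permitted concomitant medication becomes necessary during the trial, the subject should be withdrawn from the trial", and refers the reader to Section 5.4.4.
- **Section 5.4.4 (Criteria for Subject Withdrawal)** contains no rule for this event. It covers the subject's own right to leave ("Subjects will be informed that they have the right to withdraw from the trial at any time") and how a withdrawal is documented.
- **Section 5.4.5 (Withdrawal from the Trial)** names the start of a prohibited medication, and the start of another MS disease modifying therapy, under this lead-in: "Withdrawal from study treatment is mandatory in the following situations". It closes: "In case of premature withdrawal from the study treatment, the assessments scheduled for the Week 24/Exit visit should be performed".
- **Section 8.4.1 (General Considerations)** says: "Subjects who stop the Medicinal Product will be asked to remain in the study and will be analyzed with the intention to treat". The same sentence goes on to provide for a switch of drug in the model: "but adding a covariate that alternative therapies have been given". On missing values the section says: "No imputation of missing data will be performed".

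Section 5.4.6 states that "subjects prematurely withdrawn from the trial will not be replaced". Section 5.1.2 defines the primary endpoints as voxel-wise MTR change in NABT between baseline and six months.

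**The concern.** Sections 6.4.2 and 8.4.1 are both conduct instructions, and they conflict for one identifiable kind of subject: someone with RRMS who stops Rebif and moves to a listed MS drug. One instruction ends participation and the other continues it.

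What is at stake is the six-month MRI. A subject kept in the study can be scanned at Week 24. A subject taken out of the trial gets exit assessments at early termination (Section 7.2.2.3) and then only a telephone call (Section 7.2.3). With no imputation and no replacement, nothing in the protocol makes up for a Week 24 scan that was not done. A statistical analysis plan can decide how to use an early scan, but it cannot create a later one.

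**Working it through.** No figure in the protocol needs reproducing: Section 8.1 gives no power calculation. The check is a comparison of the texts, followed by two lines of arithmetic.

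**1. One subject under each rule.** Take an RRMS subject who stops Rebif before Week 23 and starts glatiramer acetate.

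| Section | Status of the subject | MRI that follows |
|---|---|---|
| 6.4.2 | should leave the trial | exit scan at early termination (5.4.7, 7.2.2.3), then a telephone call only (7.2.3) |
| 5.4.5 | leaves study treatment | Week 24/Exit assessments, with no date stated |
| 8.4.1 | asked to stay in the study, analysed as ITT with a covariate | no scan date stated; a Week 24 scan remains possible |

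**2. Can 6.4.2 and 8.4.1 be reconciled?** One could read the ban as applying only while Rebif is being taken. The text does not allow this, because the ban covers the whole trial. The covariate in 8.4.1 also presupposes subjects who remain under observation on alternative therapy. The 6.4.2 list covers the main such therapies, so following 6.4.2 would leave that covariate with few or no subjects to describe at Week 24.

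**3. Which text is out of line?** Section 5.4.5 names the same trigger, refers to 6.4.2, and asks only for withdrawal from treatment. That agrees with 8.4.1, so 6.4.2 is the outlier on trial status. Its cross-reference to 5.4.4 leads to no rule for the event.

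**4. When is a scan a six-month scan?** Inputs: Week 24 (Section 7.1) and the seven-day visit window (Section 7.1), read here as plus or minus 7 days.

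- Week 24: 24 × 7 = day 168.
- Window: 168 − 7 = day 161 and 168 + 7 = day 175.
- Lower limit in weeks: 161 / 7 = 23.

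An exit scan taken before Week 23 therefore lies outside the scheduled Week 24 window.

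**5. Weight of one subject.** Input: 25 RRMS subjects (Section 5.1.4). 1 / 25 = 0.04, or 4% of the RRMS group.

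**6. Is correcting 6.4.2 enough?** No. The closing sentence of 5.4.5 calls for the Week 24/Exit assessments on withdrawal from treatment without saying when. A site could do them all at once, MRI included, and regard the subject as finished. The six-month scan is secured only if 5.4.5 also says when the MRI is done.

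**The case against.** The strongest reply is that this is loose drafting. Section 5.4.5 is headed as withdrawal from the trial yet prescribes withdrawal from treatment, so the protocol plainly mixes the two terms, and the detailed rule for this event is the milder one. Section 6.4.2 says only what should happen. An exit MRI is prescribed in any case, and Section 8.4.3 uses the combined Week 24/Exit label as an analysis visit. The ANCOVA in Section 8.4.2 has a period effect, so a subject with a Week 12 scan still contributes. Mapping early scans to visits is ordinary analysis-plan content. Finally, the objective is the effect of Rebif, so a later scan on another drug is not obviously more informative than an earlier one.

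Much of this stands, and it limits the point. It does not remove the conflict: a site reading 6.4.2 is told to end participation and is sent to a section that does not correct this. As to which scan is more informative, the protocol has already chosen in 8.4.1: follow-up continues and the alternative therapy is modelled.

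A reader might infer more than the text supports:

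- **That the subject drops out of the primary analysis set.** Section 8.3 admits every RRMS subject with at least one injection, so ITT membership is kept.
- **That an early exit scan is discarded.** No text says that a scan before day 161 counts as missing.
- **That 6.4.2 alone costs the six-month scan.** The undated sentence in 5.4.5 could have the same effect.
- **That the result is biased in a known direction.** The protocol gives no switching rate and nothing from which direction or size could be derived.

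**Conclusion.** The inconsistency is real and should be corrected before sites act on it. For a subject who stops Rebif and starts a listed therapy, 6.4.2 says the subject should leave the trial, 8.4.1 asks the subject to stay, and 5.4.5 ends treatment only. Following 6.4.2 replaces the six-month primary-endpoint scan with an early exit scan for any withdrawal before Week 23.

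The size is modest: 4% of the RRMS group per affected subject, with the number of such subjects unknown. The conclusion assumes that the seven-day window runs in both directions and that exit assessments are done at about the time of withdrawal, as Section 7.2.2.3 indicates. It does not extend to subjects who stop Rebif without starting a listed drug, since 6.4.2 does not apply to them.

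**What to change.** Two edits by amendment.

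1. **Section 6.4.2.** Replace withdrawal from the trial with: *withdrawn from study treatment (see Sections 5.4.5 and 8.4.1)*. Drop the reference to 5.4.4.
2. **Section 5.4.5.** Keep the closing sentence, so that the non-MRI exit assessments (laboratory and thyroid tests, examinations, immunology sample, drug accountability) are still done when Rebif is stopped. Add: *A subject who stops Rebif but remains in the trial also has the remaining scheduled MRI at Week 12 and Week 24 at the planned dates, in place of an immediate exit MRI (in case of pregnancy, no gadolinium or no MRI). An immediate exit MRI is done only if the subject also leaves the trial.*

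The closing sentence of 5.4.5 should not simply be deleted. A subject stopped for a grade IV laboratory abnormality, for example, would then lose the end-of-treatment tests, and the second immunology sample could be drawn long after the last dose.

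Cost: a subject who stops before Week 12 has two further scans instead of one exit scan (2 − 1 = 1 more). A subject who stops after Week 12 has one scan either way, but on a different day from the other exit assessments. No scan is added beyond the existing schedule.
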